**Fig. 3 Fig3:**
[figure not shown]
Participant journey through the study. If the DAS28-CRP ≥ 2.4 at the screening visit, the participant is referred back to their own rheumatology team, remaining on DMARDs. All remaining participants stop their DMARDs at day 0 and are followed up with routine visits, or patient requested ad-hoc visits for 24 weeks or until the point of flare

### Confirmed flare

If a participant has a confirmed flare (DAS28-CRP ≥ 3.2, or DAS28-CRP ≥ 2.4 on 2 occasions within 14 days) an ultrasound-guided synovial biopsy will be arranged to take place within 7 days of flare confirmation. Following the synovial biopsy, the participant will receive glucocorticoid therapy if needed, and will be discharged from the study back to their referring team to rapidly recommence DMARDs. A further review (telephone call or face to face visit) will occur 4 weeks after a confirmed flare to ensure the participants’ RA is back under control, that they have had contact with their referring rheumatology team, and that they have resumed DMARD therapy. No study data will be collected at that visit.

### Participant autonomy and safety

The participant has full autonomy throughout this study. The participant information sheet makes it clear that they may withdraw their consent at any time; for example, they may opt not to stop or restart DMARD therapy when it is otherwise indicated to do so in the study protocol. The wishes of the participant will be respected, although the participant will then be discharged from the study and referred back to the clinical (referring) team.

The trial clinician may withdraw a participant from the study at any time if this is considered necessary, and for any reason including:
I.Symptomatic deteriorationII.Participant withdrawal of consentIII.Significant protocol deviation or non-compliance, including failure to attend for more than 2 consecutive visits.IV.An adverse event, such that discontinuation of DMARDs is no longer appropriate, or renders the participant unable to continue in the trialV.Termination of the clinical study by the SponsorVI.Investigator’s discretion that it is in the best interest of the participant to withdraw

Participants who withdraw from the study will not be replaced automatically as the target sample size has been calculated to allow for withdrawals.

### Clinical discretion

In certain circumstances, it may become clinically apparent that a participant has a DAS28-CRP ≥ 2.4 owing to an alternative clinical diagnosis other than their rheumatoid arthritis. Examples of this may include, but are not limited to:
I.Concurrent infection causing a rise in blood inflammatory markers or patient visual analogue scale leading to a rise in DAS28-CRP above remission thresholdsII.Local trauma event causing joint pain/swelling or a rise in patient visual analogue scale leading to a rise in DAS28-CRP above remission thresholds

In such circumstances, and after agreement with the participant, the research clinician has the discretion not to refer back to the clinical team for restart of DMARD therapy if this is felt to be clinically inappropriate. The participant should continue in the study, but should have an additional appointment review within 14 days. If the participant still has a DAS28-CRP ≥ 2.4 at this additional review, then they should normally be discharged from the study and restart their DMARDs via their referring clinical team.

Similarly, in some circumstances it may become clinically indicated to restart DMARD therapy despite the participant achieving a DAS28-CRP < 2.4 – for example, to control extra-articular manifestations of RA not measured in the remission criteria, or flaring in non-DAS28 joints, e.g. the ankles, feet. In these circumstances, the research clinician has the discretion to refer back to the clinical team for restart of DMARD therapy if this is felt to be clinically indicated at that time. The participant would then also be discharged from the study.

Furthermore, the clinician has the discretion to arrange additional investigations on clinical grounds as required in response to adverse events.

### Adverse events

Adverse events will be recorded at each study visit; the investigator will determine the severity as mild, moderate or severe, and ascertain any causal relationship with the study intervention. Any serious adverse events will be reported immediately to the chief investigator who will inform the Sponsor and the Research Ethics Committee (REC). A serious adverse event is any adverse event which:
Results in deathIs life-threatening (i.e. an event in which the participant was at risk of death at the time of the event; it does not refer to an event which hypothetically might have caused death if it were more severe)Requires hospitalisation, or prolongation of existing hospitalisationResults in persistent or significant disability or incapacityIs a congenital anomaly or birth defect

Following cessation of DMARD therapy, we expect that approximately half of the participants will experience a confirmed flare of their arthritis requiring resumption of DMARD therapy and potentially temporary glucocorticoid treatment, without the need for hospitalisation. We also expect that participants who consent to synovial biopsy may experience temporary symptoms (24–48 h) of mild joint pain, swelling or bruising at the biopsy site, but that this is a safe and well tolerated procedure [17]. Joint pain, joint swelling and joint stiffness will not be recorded as an adverse event throughout the BIO-FLARE study.

### Pregnancy

Pregnancy is associated with a diverse range of physiological changes, and is often associated with a reduction in rheumatoid arthritis activity. Pregnancy can therefore be expected to greatly influence the underlying pathogenic processes in RA and any associated biomarkers, and thus pregnancy is an exclusion criterion for this study.

Where pregnancy in a female participant becomes apparent after the enrolment of the participant to the study, this must be recorded as an adverse event. The participant’s referring rheumatologist and GP must be informed, and then the participant must be discharged from the study, remaining off DMARD therapy. The progress of the pregnancy should be followed to term, with no additional follow-up required if the neonate is healthy at birth.

Where the female partner of a male study participant becomes pregnant during study participation, this should also be recorded as an adverse event. The participant may continue within the study. The progress of the pregnancy should be followed to term, with no additional follow-up required if the neonate is healthy at birth.

### Trial governance

The trial management group (TMG) functions to provide operational oversight of the entire BIO-FLARE project including patient recruitment, clinical procedures, laboratory procedures and finance. Any changes to the study Protocol, Participant Information Sheet, Consent Form or Standard Operating Procedures must be reviewed and authorised by the TMG prior to implementation.

As this is a non-CTIMP study, a Combined Trial Oversight Committee (CTOC) will subsume the roles of a Trial Steering Committee (TSC) and Data Monitoring and Ethics Committee (DMC). The CTOC provides independent oversight of the BIO-FLARE project, particularly with regard to patient recruitment and safety. Independence is to be maintained by the use of open and closed sessions for the CTOC and by limiting the voting rights of the non-independent representatives.

### Statistical considerations

The aims of the statistical analyses are to estimate and understand the longitudinal stochastic relationship between the risk of flare and each of the markers in the relevant biological pathways. The overall proportion (confidence interval) of participants who flare by 24 weeks will be estimated using the actual time of flare based on Kaplan-Meier estimates. Graphical representation and descriptive statistics of the longitudinal marker measurements will indicate trends in markers over time, to identify plausible differences in trends in participants who flare and those who do not.

The association between markers and risk of flare will be investigated in a series of descriptive univariate models, based on analysis of each covariate in Cox proportional hazards models, or parametric alternatives, with time varying covariates to account for the longitudinal nature of marker data, through attributing variability at the participant level, time level and marker level. Individual covariates may not be linear in their relationship with outcome so the ‘best’ fitting non-linear relationship will be explored using Fractional Polynomial transformation [18]. The magnitude of the relationship of each marker with risk of flare will be described using estimated beta coefficients (with confidence intervals) accounting for variability at the time level and marker level.

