**Methods:**

The BIO-FLARE study is a non-randomised longitudinal cohort study that aims to enrol 150 patients with RA in remission on a stable dose of non-biologic disease-modifying anti-rheumatic drugs (DMARDs), who consent to discontinue treatment. Participants stop their DMARDs at time 0 and are offered an optional ultrasound-guided synovial biopsy. They are studied intensively, with blood sampling and clinical evaluation at weeks 0, 2, 5, 8, 12 and 24. It is anticipated that 50% of participants will have a disease flare, whilst 50% remain in drug-free remission for the study duration (24 weeks). Flaring participants undergo an ultrasound-guided synovial biopsy before reinstatement of previous treatment. Blood samples will be used to investigate immune cell subsets, their activation status and their cytokine profile, autoantibody profiles and epigenetic profiles. Synovial biopsies will be examined to profile cell lineages and subtypes present at flare. Blood, urine and synovium will be examined to determine metabolic profiles. Taking into account all generated data, multivariate statistical techniques will be employed to develop a model to predict impending flare in RA, highlighting therapeutic pathways and informative biomarkers. Despite initial recruitment to time and target, the SARS-CoV-2 pandemic has impacted significantly, and a decision was taken to close recruitment at 118 participants with complete data.

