Ultrasound assessment for Synovial Biopsy (OPTIONAL AT BASELINE – additional consent required)			[X]								X
Accelerometer provided^c^ (OPTIONAL)	X										
Activity diary provided (OPTIONAL)	X			X	X	X	X		X		

^a^Depending on the circumstances of the consultation, physical examination may be indicated at any study visit to establish whether DAS28-CRP reflects arthritis activity or infection etc. General Physical Examination is only mandatory at Screening

^b^Mandatory at Screening but should be performed at any visit subsequently if routine questioning suggests a participant may be pregnant. Serum or urine tests to be performed subsequently in line with local policy

^c^This may be provided after the study visit once eligibility confirmed, either by post, or at the optional Baseline Synovial Biopsy Visit (if applicable)

Following this visit, the disease activity score in 28 joints with C-reactive protein (DAS28-CRP) is calculated. The cut off for remission was set at DAS28-CRP < 2.4. This is lower than some other remission guidelines given the knowledge that DAS28 values calculated using CRP are commonly lower than those using ESR [15, 16]. If the DAS28-CRP score is < 2.4 and the participant has declined the optional baseline synovial biopsy, then the participant is advised to immediately discontinue their DMARD therapy. Participants who have a DAS28-CRP < 2.4 and have provided additional consent for an optional baseline synovial biopsy will be invited to attend for an additional biopsy visit at their regional Hub site. They will stop their DMARD treatment after the biopsy has been performed. If the DAS28-CRP score is ≥2.4 then the participant is withdrawn from the study at this point, they are referred back to their rheumatology team, and DMARD therapy is continued.

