### Follow-up period – day 14, 35, 56, 84, 168 and ad hoc visits

At routine visits, adverse event recording and current medications are noted. Clinical and research blood and urine tests are taken and questionnaires are completed. A joint examination is performed to allow calculation of a DAS28-CRP.

If a participant feels that their arthritis is becoming more active during the follow-up period, then they can arrange an ad hoc visit. These visits follow the same format as the routine visits.

At any point in the study period if the participant is found to have a DAS28-CRP ≥ 3.2 they are defined as having a confirmed flare. If a participant is found to have a DAS28-CRP ≥ 2.4 but < 3.2 they will return for a further ad hoc assessment within 14 days. At the second assessment if the DAS28-CRP ≥ 2.4 they will be defined as a confirmed flare (Fig. 3).

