The design of the BIO-FLARE study allows a participant to be closely monitored in the period immediately prior to clinical onset of flare. Clinical determinants are collected and tracked over time, such as CRP, joint counts and RAPID-3 scores, along with biological outcomes. At each participant visit, blood is taken for research, processed following SOPs and stored, with the sample location information recorded in a laboratory inventory management system (LIMS). The downstream analysis of this blood will allow multiple questions to be explored. Epigenetic profiling of PBMCs and CD14+ monocytes will be conducted allowing comparison to those who stay in remission. Whole blood and PBMCs will be analysed by flow cytometry to provide deep immune-phenotyping of the samples. Serum and urine samples will be used for metabolic profiling, and autoantibody profile and cytokine levels will also be investigated using serum samples. Synovial tissue collected at the point of flare will be analysed and, in certain cases, can be paired with samples from the same participant whilst in remission, prior to DMARD cessation.

The impact of the SARS-CoV-2 pandemic has had far reaching consequences for all aspects of medical care, including non-COVID research. After extensive discussions amongst the Trial Management Group, including statisticians, the decision was made to close recruitment at 118 participants to enable timely data analysis. Strategies to lessen the impact caused by the reduced sample size on power will be considered including, for example, restricting the number of biomarkers to be considered in a multivariable risk model.

In summary, the novel nature of this study will allow deep interrogation of the mechanisms occurring in the days and weeks leading up to the point of RA flare. Our aim is to further the understanding of the pathophysiology of flare, develop strategies for intervention, and also to prevent or predict flare. Furthermore, these same mechanisms may also be at play during the onset of RA, and thus may also serve to further our understanding of the immunopathology of early stages of the disease.

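### Flare is an absolute DAS28-CRP level that starts at the entry cut-off of 2.4, so unadjusted marker coefficients may partly reflect how near participants start to the threshold

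*Protocol article*

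**What the plan says.** **Entry.** The protocol article, Screening visit, states: "The cut off for remission was set at DAS28-CRP < 2.4". Participants at or above that value are withdrawn and stay on treatment.

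**Event.** The Follow-up period section gives two routes. On the first, "if the participant is found to have a DAS28-CRP ≥ 3.2 they are defined as having a confirmed flare". On the second, a score from 2.4 to below 3.2 leads to a repeat assessment within 14 days: "At the second assessment if the DAS28-CRP ≥ 2.4 they will be defined as a confirmed flare". The Confirmed flare section restates both: "confirmed flare (DAS28-CRP ≥ 3.2, or DAS28-CRP ≥ 2.4 on 2 occasions within 14 days". Both routes are absolute levels, and neither contains a change from baseline.

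**Discretion.** The Clinical discretion section lets the clinician act differently where "a participant has a DAS28-CRP ≥ 2.4 owing to an alternative clinical diagnosis other than their rheumatoid arthritis", for example with infection or trauma.

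**Analysis.** Statistical considerations sets out the association of markers with flare risk "in a series of descriptive univariate models, based on analysis of each covariate in Cox proportional hazards models", or parametric alternatives, with time-varying marker values. The size of each relationship is to be described by beta coefficients with confidence intervals. No adjustment covariate is named there. Elsewhere the article plans a joint model: the Abstract says "multivariate statistical techniques will be employed to develop a model to predict impending flare in RA", and the Discussion mentions "restricting the number of biomarkers to be considered in a multivariable risk model". Neither place lists the covariates.

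**The concern.** On the two-reading route, the rise needed to become an event is 2.4 minus the starting score. Someone who enters at 2.3 needs 0.1; someone who enters at 1.4 needs 1.0. Starting activity therefore influences event status partly by construction, in two ways. Participants near 2.4 can cross it through ordinary variation, and participants who start low can have a genuine rise that never reaches 2.4.

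A marker correlated with residual activity, such as CRP, a cytokine or a cell-activation measure, inherits that association even if it says nothing about the transition to flare. A one-covariate hazard ratio cannot separate the two explanations. The separation matters for the objectives. The primary objective concerns immune dysregulation immediately before flare, and a secondary objective is to corroborate baseline biomarkers of sustained drug-free remission. Both could be answered partly with markers of starting close to the cut-off.

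**Working it through.** **1. The plan's own figures.** The earlier withdrawal study had 23/44 = 52.3% flares, which agrees with the stated 52%. At the anticipated 50%, 118 participants give 0.5 × 118 = 59 events, against 0.5 × 150 = 75 at the planned size. The article gives no figure for the variability of DAS28-CRP, so what follows rests on assumptions.

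**2. Chance of a confirmed flare with no true change.** Assume a stable true score m, independent normal readings with within-person SD s, and five scheduled visits (days 14, 35, 56, 84, 168). Let p = P(reading ≥ 2.4) and q = P(reading ≥ 3.2).

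- Per visit: f = q + (p − q)p, that is, one reading of at least 3.2, or one from 2.4 to below 3.2 followed by another of at least 2.4.
- Over five visits: 1 − (1 − f)^5.

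For s = 0.4:

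- m = 2.2: p = 0.309, q = 0.006, f = 0.006 + 0.302 × 0.309 = 0.0995, and 1 − 0.9005^5 = 41%.
- m = 1.8: p = 0.067, q = 0.0002, f = 0.0047, and 1 − 0.9953^5 = 2%.

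| Assumed s | m = 2.2 | m = 1.8 |
|---|---|---|
| 0.3 | 28% | 0.3% |
| 0.4 | 41% | 2% |
| 0.6 | 60% | 16% |

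Ad hoc visits would add chances. Correlation between a reading and its repeat, and clinical discretion, would change these figures.

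**3. Effect on a marker coefficient.** Cohorts of 118 were simulated (200 per scenario, 16 scenarios) with the protocol's visit days, entry rule and both flare routes. Assumed, and not in the article:

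- underlying level with mean 1.7 and SD 0.4
- within-person SD 0.2 to 0.5
- a true rise of 1.5 in 30% or 45% of participants, independent of marker and baseline
- a baseline marker correlated 0.3 or 0.5 with the underlying level and otherwise unrelated to flare.

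| Result | All 16 scenarios | True rise in 45% (flare proportion 45% to 47%) |
|---|---|---|
| Confirmed flares with no true rise | 6% to 29% | 6% to 20% |
| Marker alone: HR per SD | 1.08 to 1.28 | 1.08 to 1.24 |
| Marker alone: p<0.05 | 8% to 35% | 8% to 31% |
| Adjusted for screening score: HR per SD | 1.02 to 1.23 | 1.02 to 1.19 |
| Adjusted: p<0.05 | 5% to 24% | 5% to 21% |

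The nominal rate is 5%. The Monte Carlo standard error is about √(0.08 × 0.92/200) = 1.9 points at 8% and √(0.35 × 0.65/200) = 3.4 points at 35%. Screening DAS28-CRP itself had a hazard ratio of 1.21 to 1.43 per SD in the adjusted models.

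**4. Cost in precision.** In a further run, the standard error of the marker's log hazard ratio rose on adjustment from 0.148 to 0.155 (within-person SD 0.4) and from 0.146 to 0.151 (SD 0.5). Adjustment reduces bias; it does not sharpen the estimate.

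**The case against.** **The univariate models are descriptive, and a joint model is planned.** This largely stands. A reader might infer that baseline DAS28-CRP is left out of the whole analysis. The article does not support that: it announces a multivariable model without listing its covariates, and that list commonly sits in the analysis plan, which is not at hand. The point is confined to the coefficients in Statistical considerations, whose form the article does fix.

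**2.4 is not a one-touch threshold.** This is correct. It needs a second reading within 14 days, and the single-reading route at 3.2 requires a rise of more than 0.8 from any eligible entry score. Step 2 includes both routes. Clinical discretion deals with raised scores that have another diagnosis, and does not clearly reach ordinary variation around 2.4.

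**The numbers are assumed.** This stands. A reader might infer that markers of residual activity will look like predictors. In most simulated cohorts the null marker did not reach significance, so only *may* is supported. The simulated marker was also a baseline one, whereas the article plans time-varying values.

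**Residual inflammation may be part of the biology sought.** This is fair. Unadjusted and adjusted coefficients answer different questions, and a descriptive unadjusted association is no error in itself. It is a reason to report both. CRP and joint counts are components of the score, so adjusting them for it partly adjusts a marker for itself.

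**Conclusion.** The point holds as a limited one. The article defines flare by absolute levels, lets one route begin at the entry cut-off with no minimum rise, and describes marker effects by one-covariate coefficients. Markers of residual activity may therefore show an association with flare that comes partly from starting near 2.4.

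Under the assumptions in step 3 the distortion is modest per marker (mean HR per SD 1.08 to 1.28 where the true marker effect is nil). It is still enough to raise the false-positive rate from 5% to between 8% and 35%. These figures depend on within-person variability, the distribution of entry scores and the marker's correlation with activity, none of which the article gives. The documents do not show that the planned multivariable model shares the problem, nor that any particular marker will be affected.

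**What to change.** 1. Beside each univariate model, report the same marker coefficient adjusted for screening DAS28-CRP as a continuous covariate. Interpret CRP and other components of the score with care.
2. State that screening DAS28-CRP will be carried into the planned multivariable risk model.
3. As an analysis-only sensitivity check, repeat the marker models counting as events only flares that also show a prespecified minimum rise from the screening score. The clinical flare rule stays as it is.

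**Cost.** The score is already collected on everyone at screening, so no design change is needed. Each adjusted model spends one degree of freedom and has a slightly larger standard error (step 4).

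**Limits.** Adjustment removes only part of the artefact, because a single screening score measures the underlying level with error. The minimum-rise check uses the same score. Participants who meet the clinical rule without the minimum rise leave the study at that point, so their censoring is informative. It should be read as a check on direction and not as a replacement analysis.
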